#### H1: Sample Size, Power, and Analysis

Although we plan for 180 agencies to compose the total sample size, only 120 (66.7%) will be allocated to arms 1 (n=60) and 2 (n=60), meaning that the sample size for this hypothesis is 120. With 60 agencies in each arm, we will have 80% power to detect significant differences (2-tailed α=.05) between arms 1 and 2 in the proportions of agencies that are successfully recruited if the difference in proportions is at least 0.25 (eg, 18/60, 30% recruited in arm 1 vs 33/60, 55% recruited in arm 2). The primary analysis will be conducted using logistic regression, comparing the recruitment rate between the arms. We will report exact P values and commit to a cautious interpretation of the findings, avoiding overreliance on P values as the single arbiter of meaning [64]. We do not expect any missing data in the outcome variable because the nature of its computation is such that missing data mean that either *A*=*0* or *R*=*0* and are therefore built into outcome variable *M*.

The primary study outcome (*M*) will be tested separately for the periods 6 and 12 months after initial recruitment correspondence. Analysis covariates are planned to include, but may not be limited to, community rurality and the community’s percentage vote share for the Republican candidate in the 2020 presidential election (available for 2523 US counties and separable by zip code [65]), given that political orientation was 1 of 2 strongly predictive variables in our regression model examining misperceptions of OEND [39].

### H2: Layperson Responders

#### Overview

Layperson responders who are part of the *PulsePoint* system register with a local first responder agency using their smartphone. Most layperson responders (eg, those who are not also off-duty first responders themselves) are only alerted to incidents in public spaces. No identifying information is collected from these users except the unique ID of the device.

The first responder agency in each community that manages the *PulsePoint* subscription can only determine the number of active users and, broadly, the type of smartphone being used (eg, Android smartphone or iPhone). Each time a first responder agency sends out a push notification, it is provided with an exact count of the number of unique devices, separated by type, that were active in the system and reached by the message.

It is important to note that we will have a count of unique active devices but not necessarily a count of unique active users (eg, it is unlikely but possible that someone will install the app on 2 different mobile phones at the same time). In correspondence with the PulsePoint Foundation, it is likely that the count of unique active devices serves as a very close approximation of unique active users. Furthermore, by virtue of randomization, the distribution of any unmeasured anomalies related to user-device mismatches should be evenly distributed across the arms.

#### Conceptualizing Recruitment for Layperson Responders

Currently, for a *PulsePoint* user to be officially recruited as a CPR responder and to be sent notifications regarding unconscious and unresponsive persons in public places, they need to affirmatively indicate that they are trained in CPR *and* are “willing to assist in case of an emergency.” Individuals who so verify are sent push alerts and auditory alert tones, regardless of whether the app is open, whenever there is an unresponsive and unconscious person within a specific radius of their mobile phone (the radius is specified by the first responder agency for that community) [66].

For the purposes of this study, a layperson responder will be considered to have been recruited for *PulsePoint-OD* if they certify that they have received training on overdose and naloxone and that they currently carry naloxone on their person (both outcomes are of interest, which we describe later in the *Outcome Variables and Measurement* section). Once an MOU is in place with a first responder agency, it will send out a customized baseline push message to all active users containing a link to a landing page. This page will contain brief introductory text explaining the importance of recognizing an overdose when responding to unconscious persons and the efficacy of naloxone, as well as 2 questions asking them to indicate, by pressing radio buttons, whether they have received training on recognizing an overdose and administering naloxone and whether they currently carry naloxone on their person. Additional push messages encouraging users to respond to the certification questions will be sent twice within the month to maximize the number of participants providing baseline data. A user’s responses to these questions will not change their status within the app or the behavior of the app because all users are already alerted to unresponsive or unconscious persons who may have experienced an overdose. This certification procedure will be repeated twice (6 months and 12 months after the baseline certification requests are sent). These messages will emphasize that even users who have previously provided such information should do so again.

The *PulsePoint* app is structured in such a way that push notification hyperlinks can open an external web page in a web browser window inside the app. Using the style guides and templates from the PulsePoint Foundation, the certification web pages will be designed to be similar to the appearance of the app to avoid disrupting the user experience while avoiding cross-contamination of messaging between the study arms. Each web page will be accessible only via the hyperlink in its associated push notification, and users will not be able to navigate among web pages or access the web pages for other study arms.

As multiple data collection reminders will be sent each time (baseline, 6 months, and 12 months), we want to minimize the likelihood of an individual repeatedly certifying their involvement. This risk exists because of the completely anonymous way that individual *PulsePoint* users are managed by the system. Thus, the landing page will be configured to store a cookie [67] on the mobile device. Although cookies are typically perceived as tracking devices, this cookie will not *record anything except whether the user has previously responded to either question on the landing page* during the data collection cycle, and it will be programmed to delete itself after each data collection period (eg, 3 weeks). When users who have already completed the questions return to the landing page, the cookie will prevent the questions from being displayed, although we anticipate that some of the users may clear their smartphone browser cache or actively prevent the use of cookies.

#### Layperson Intervention (Recruitment) Arm 1

Users randomized to arm 1 will receive standard monthly recruitment push messages. These push messages will differ from the certification messages because they will contain language intended to foster engagement with OEND services (eg, to get trained and carry naloxone) alongside the link to a landing page (eg, “Are you trained to recognize an overdose? Be a community hero! Click here for more information!”). The messages will be developed based on best practice recruitment principles in cooperation with an external marketing team and then reviewed and finalized by the study team. Messages will be different each month. The monthly time frame was selected based on our need to balance contact with responders and research or expert opinions on push messaging saturation. In a hypothesis-driven objective measure study, increased push messaging frequency was associated with additional app uninstalls *and* lower push message opening rates [68]. This information is generally consistent with the much larger volume of layperson marketing gray literature on push notification optimization (eg, *how-to* blogs [69]). Figure 3 displays the planned timing of the recruitment and data collection messages.

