#### Hypotheses

We will test the following hypotheses:

H1: more first responder agencies will be successfully recruited by arm 2 than by arm 1.H2: more layperson responders will report engaging with OEND programming in arm 2 than in arms 1 or 3 and in arm 1 than in arm 3.

As an exploratory follow-up, we will conduct incentivized qualitative follow-up interviews with agencies to better understand barriers to participation and how to improve uptake feasibility.

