**Figure 3 figure3:**
[figure not shown]
Push notification types and timing relative to agency recruitment. B: baseline.

The landing page for recruitment will be updated to include a link to the Community Overdose Responder naloxone training [70], which has been designed specifically for laypersons and integrates elements of OEND programming and *PulsePoint*. Where provided by community first responder agencies, we will also include a list of ways to obtain free or reduced-cost naloxone locally as well as information about upcoming local OEND events. Separately, we note that accessing at-cost naloxone (ie, not free or subsidized) will be relatively easy, in principle, given its transition to OTC status [22].

#### Layperson Intervention (Recruitment) Arm 2

As in the case of the differentiation between agency recruitment in arm 1 and arm 2, the recruitment of layperson responders for arm 2 will follow the same procedures that are described for arm 1 but will use separate messaging. Specifically, the push messages and landing page will contain additional, brief messages that specifically provide factual information that counteracts misperceptions about overdose and naloxone [39]; for example, whereas an example message for arm 1 might be “Are you trained to recognize an overdose? Be a community hero! Click here for more information!” the permutation for arm 2 might be “Are you trained to recognize an overdose? Studies show that most people revived with naloxone will not overdose again within the next year! Click here for more information!”

#### Layperson Intervention (Control) Arm 3

Arm 3 functions as the control arm and will not receive any monthly recruitment messaging or encouragement, but laypersons will still be asked, using push notifications, to provide information at baseline and 6 and 12 months later to document whether they have been trained to recognize an overdose and administer naloxone and whether they currently carry naloxone on their person (eg, “Please let us know whether you have ever been trained to recognize an overdose or if you carry naloxone by clicking here.”). The landing page will likewise contain the questions with radio button responses but will not link to training opportunities or contain additional information.

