#### Outcome Variables and Measurement

In H2, we hypothesize that more layperson responders will indicate that they have received OEND programming and carry naloxone on their person within 6 and 12 months of initial contact using procedures in arm 2 (tailored messaging) compared to procedures in arm 1 (standard messaging) and using procedures in either arms 1 or 2 versus arm 3 (control). We will use several different data points to assess our hypothesis.

All push notifications sent out by first responder agencies already return information through the *PulsePoint* app indicating the total number of active devices, by type, that were messaged. As we explained previously, this is a strong proxy measure for the total number of active users messaged because most people use a single smartphone.

For purposes of computation, this total number of recipients of any push notification will be designated as *T*. Next, the total number of individuals who click on the pushed link will be represented by *O*, which will be a number between *0* and *T*. Importantly, the link will also be coded using HTML and CSS so that it sends additional data when clicked, indicating the originating community (cluster identity) and the data collection point (*D*, a value ranging from *0*, which is the initial push message cluster, to *2*, which is the final data collection message set at 12 months after baseline). Subsequently, the number of instances of an individual (ie, unique device) indicating that they have been trained on recognizing an overdose and administering naloxone (represented by *N*, a binary value of *0* or *1*) and whether they currently carry naloxone (represented by *C*, also a binary value of *0* or *1*) will be captured from the landing page itself.

This information will allow us to determine the following, separately by community:

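### The H2 training item has no time window, so follow-up X measures training at any time rather than engagement with OEND, which mainly dilutes the arm contrast

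*Protocol article*

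**What the plan says.** In the Protocol article, Hypotheses states H2 as "more layperson responders will report engaging with OEND programming in arm 2 than in arms 1 or 3", with arm 1 also expected to exceed arm 3. The H2 section Outcome Variables and Measurement restates it: more responders will indicate that "they have received OEND programming and carry naloxone on their person within 6 and 12 months of initial contact".

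The measurement is described in three places:

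- Conceptualizing Recruitment for Layperson Responders: the landing page asks "whether they have received training on recognizing an overdose and administering naloxone and whether they currently carry naloxone on their person".
- Layperson Intervention (Control) Arm 3: the example message reads "Please let us know whether you have ever been trained to recognize an overdose or if you carry naloxone by clicking here".
- Outcome Variables and Measurement (H2): N counts devices "indicating that they have been trained on recognizing an overdose and administering naloxone", and X = N/T at D = 0, 1 and 2, where T is the number of push recipients.

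On repetition, the article says "This certification procedure will be repeated twice (6 months and 12 months after the baseline certification requests are sent" and adds "These messages will emphasize that even users who have previously provided such information should do so again". Users are anonymous. The cookie stores only whether the user has responded in the current collection cycle and is then deleted.

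The H2 section Sample Size, Power, and Analysis names X and Y as the primary metrics. It plans generalized linear mixed models with Z = O/T as a covariate and possibly others. It gives 80% power for f=0.21 (50 communities per arm) to f=0.34 (20 per arm), with three time points and a correlation of 0.5.

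**The concern.** H2 describes something the messages are meant to bring about, whereas the item records a status that may long predate them. A user trained years ago, such as one of the off-duty first responders mentioned in the H2 Overview, scores N=1 at both follow-ups in every arm without doing anything in the trial. An already trained user who takes the linked course because of the messages adds nothing, since N is already 1.

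X is one of two primary metrics for H2. If prior training is common, a real difference in uptake between arms will look small in X. With anonymous, unlinked responses, the date of training cannot be recovered later if it was never asked.

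**Working it through.** **1. Reproducing the stated power.** Inputs from the H2 power section: 3 arms, m=3 waves, rho=0.5, two-tailed alpha 0.05, N=150 or 60 agencies. For a between-arm effect averaged over all waves, the noncentrality is f²·N·m/(1+(m-1)·rho), with 2 and N-3 df.

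- N=150: f²·150·3/2 = 225f². Power of 80% needs f=0.209; power at the stated 0.21 is 80.4%.
- N=60: f²·60·3/2 = 90f². Power of 80% needs f=0.336; power at the stated 0.34 is 81.0%.

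The alternatives do not match. An arm-by-time interaction gives 0.116 and 0.186, and a single wave gives 0.256 and 0.411. The stated figures are therefore correct for an arm average over three waves, baseline included.

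**2. What X contains at follow-up.** Let r be the share of recipients who answer, b the share of those already trained before the baseline request, and q the share newly trained. Then X = r·(b + (1-b)·q), and the arm 2 minus arm 1 difference is r·(1-b)·(q2-q1). If trained and untrained users take the course equally often, engagement itself would differ by r·(q2-q1), so X shows only the fraction (1-b). If only untrained users took it, the absolute difference would be unchanged and only the ratio diluted.

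**3. Size, with assumed values.** The documents give neither b nor q. Take q = 2%, 10% and 15% in arms 3, 1 and 2. New training alone then has ratios 15/10 = 1.50 (arm 2/arm 1) and 10/2 = 5.0 (arm 1/arm 3). In X, r cancels when it is equal across arms. For b=30%, arm 1 is 0.30+0.70·0.10 = 0.370, arm 2 is 0.30+0.70·0.15 = 0.405, and 0.405/0.370 = 1.09.

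| b | arm 2/arm 1 | arm 1/arm 3 | factor (1-b) | arm 1 N from prior training |
|---|---|---|---|---|
| 10% | 1.24 | 1.61 | 0.9 | 53% |
| 20% | 1.14 | 1.30 | 0.8 | 71% |
| 30% | 1.09 | 1.18 | 0.7 | 81% |
| 50% | 1.05 | 1.08 | 0.5 | 91% |

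**4. What a follow-up contrast would detect.** Suppose the arms are equal at baseline and differ by the same amount at both follow-ups. The three-wave average then carries 2/3 of the follow-up effect, so f=0.209 and 0.336 on the average require 0.209·1.5 = 0.314 and 0.336·1.5 = 0.504 at follow-up. One follow-up wave adjusted for baseline X, at the plan's correlation of 0.5, has residual variance 1-0.5² = 0.75. The detectable f is then about 0.256·√0.75 = 0.222 and 0.411·√0.75 = 0.356, ignoring the one df spent on the covariate.

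**The case against.** There is a fair case for the plan as written. The phrase about 6 and 12 months can date the report rather than the training, as it dates agency agreement in H1, and it also covers carrying naloxone, which is a current status. The operational definitions consistently describe a status, and a status suits the stated goal of having trained people nearby. Randomization should balance prior training. The same item is asked at baseline in all arms, so an agency-level adjustment needs no person-level linkage, and a condensed article may leave the exact contrast to the analysis plan.

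Much of this stands. The time phrase is ambiguous rather than a flat contradiction, the status measure is worth keeping, and dilution is the main consequence. What remains is that Hypotheses speaks of engaging with programming, the item cannot show it, and the one contrast that the article's figures imply includes baseline.

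Two stronger readings are tempting but unsupported:

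- A reader might infer that X could rise when nobody is newly trained. With an assumed b=40%, a change in response from 10% to 12% moves X from 0.10·0.40 = 4.0% to 0.12·0.40 = 4.8%, against 0.10·0.60·0.05 = 0.3 points from training 5% of the untrained. But that rise comes from an assumed response change. It is a property of N/T that affects Y equally, and Z is planned as a covariate for push engagement. It also partly survives rewording: 0.10·0.60·0.05 = 0.30% becomes 0.12·0.60·0.05 = 0.36%, the same 20% relative inflation.
- A reader might infer that prior training is known to be large. No prevalence is given, and off-duty responders are described as the exception among users.

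**Conclusion.** The point holds as a mismatch between H2 and its training measure. Follow-up X is the prevalence of self-certified training at any time. Under balanced prior training, the absolute arm contrast is multiplied by (1-b), on the assumption that already trained users engage as often as others. For b from 10% to 50% and the assumed uptake above, a true arm 2/arm 1 ratio of 1.50 appears as 1.24 down to 1.05.

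Bias, as opposed to dilution, is possible but not shown. H2 uses only agencies that agree, and the Discussion calls agreement in arm 3 uncertain. Arms 1 and 2 receive monthly messages and arm 3 none, so who stays on the app and who answers may also differ.

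The stated power arithmetic is not wrong; it answers a question about an average that includes baseline. Y is not touched by this wording. The explicit word for lifetime training appears only in the arm 3 example; for arms 1 and 2 it follows from the absence of any window.

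**What to change.** In all three arms:

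- Keep the existing training item at D=0, 1 and 2 as a repeated status measure.
- At D=1 and D=2 add one item anchored to the baseline request, for example: *Since [month of the baseline request], have you completed training on recognizing an overdose and giving naloxone?* Define the H2 engagement outcome from it. Anchoring to baseline rather than to the previous request means that training in months 0 to 6 still counts at 12 months.
- Test status X as the arm contrast at 6 and 12 months adjusted for agency-level baseline X, not as an average that includes baseline.
- Restate the detectable effect for the follow-up contrast. For status X, step 4 of the working suggests about f=0.22 to 0.36 per wave. The new item's correlation with baseline X is unknown, so the unadjusted 0.256 to 0.411 is the cautious figure for it.

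The cost is one extra radio-button item, some recall error over up to 12 months, and a revised power statement. The Results section reports no data collection at submission, so the change could be made then without loss of data. The new item does not remove the dependence of N/T on response rates, which needs separate handling.

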**Figure 3 figure3:**
[figure not shown]
Push notification types and timing relative to agency recruitment. B: baseline.

The landing page for recruitment will be updated to include a link to the Community Overdose Responder naloxone training [70], which has been designed specifically for laypersons and integrates elements of OEND programming and *PulsePoint*. Where provided by community first responder agencies, we will also include a list of ways to obtain free or reduced-cost naloxone locally as well as information about upcoming local OEND events. Separately, we note that accessing at-cost naloxone (ie, not free or subsidized) will be relatively easy, in principle, given its transition to OTC status [22].

#### Layperson Intervention (Recruitment) Arm 2

As in the case of the differentiation between agency recruitment in arm 1 and arm 2, the recruitment of layperson responders for arm 2 will follow the same procedures that are described for arm 1 but will use separate messaging. Specifically, the push messages and landing page will contain additional, brief messages that specifically provide factual information that counteracts misperceptions about overdose and naloxone [39]; for example, whereas an example message for arm 1 might be “Are you trained to recognize an overdose? Be a community hero! Click here for more information!” the permutation for arm 2 might be “Are you trained to recognize an overdose? Studies show that most people revived with naloxone will not overdose again within the next year! Click here for more information!”

#### Layperson Intervention (Control) Arm 3

Arm 3 functions as the control arm and will not receive any monthly recruitment messaging or encouragement, but laypersons will still be asked, using push notifications, to provide information at baseline and 6 and 12 months later to document whether they have been trained to recognize an overdose and administer naloxone and whether they currently carry naloxone on their person (eg, “Please let us know whether you have ever been trained to recognize an overdose or if you carry naloxone by clicking here.”). The landing page will likewise contain the questions with radio button responses but will not link to training opportunities or contain additional information.

